## ABBREVIATIONS AND SYMBOLS USED

|                  |                                                 |
|------------------|-------------------------------------------------|
| 95% CI           | 95% Confidence Interval                         |
| ALAT             | Alanine-Amino-Transferase                       |
| ASAT             | Asparagine-Amino-Transferase                    |
| BPRC             | The Biomedical Primate Research Center          |
| CRF              | Case Report Form                                |
| D n   | Day n                                           |
| EC               | Ethics Committee                                |
| ELISA            | Enzyme-linked Immunoassay                       |
| ELISPOT          | Enzyme Linked ImmunoSpot                        |
| EMVI             | European Malaria Vaccine Initiative             |
| FVO              | Vietnam Oak Knoll                               |
| GCP              | Good Clinical Practice                          |
| PIA              | Plasmodium Inhibition Assay                     |
| γGT              | γ-Glutamyl-Transpeptidase                       |
| GMT              | Geometric Mean Titer                            |
| HBV              | Hepatitis B Virus                               |
| HCV              | Hepatitis C Virus                               |
| HIV              | Human Immunodeficiency Virus                    |
| IFA              | Immuno-Fluorescence Assay                       |
| IFN γ | Interferon γ                                    |
| IgG              | Immunoglobulin G                                |
| IL-4             | Interleukine-4                                  |
| INN              | International Non-proprietary Name              |
| IRB              | Institutional Review Board                      |
| IRAEF            | Initial Report for Adverse Event Form           |
| MCH              | Mean Corpucular Haemoglobin                     |
| MCHC             | Mean Corpuscular Haemoglobin Concentration      |
| MCV              | Mean Corpuscular Volume                         |
| MW               | Molecular Weight                                |
| NIMR             | National Institute of Medical Research - London |
| Pf               | Plasmodium falciparum                           |
| RBC              | Red Blood Cell Count                            |
| SAE              | Serious Adverse Event                           |
| UMCN             | University Medical Centre Nijmegen              |
| WBC              | White Blood Cells                               |
| WHO              | World Health Organization                       |

[figure not shown]

## 1 BACKGROUND INFORMATION

### 1.1 Introduction

Malaria is a common and serious tropical disease. It is a protozoal infection transmitted to human beings by mosquitoes biting mainly between sunset and sunrise. Human malaria is caused by four species of Plasmodium protozoa: *Plasmodium falciparum*, *P. vivax*, *P. ovale* and *P. malariae*. Malaria is a public health problem in over 90 countries worldwide, inhabited by some 40% of the world population, i.e. over 2 billion people. It has been estimated that the incidence of malaria in the world may be in the order of 300 million clinical cases each year. Countries in tropical Africa account for more than 90% of these cases. Malaria mortality is estimated at more than 1 million deaths worldwide per year. Most malaria deaths occur among young children in Africa, especially in remote rural areas with poor access to health services. Other high-risk groups include women during pregnancy, and non-immune travellers, refugees, displaced persons, or labour forces entering into endemic areas. Malaria infection has been increasing over recent years due to a combination of factors including increasing resistance of malarial parasites to chemotherapy and increasing insecticide resistance of the *Anopheles* mosquito vector, ecological and climate changes, increased international travel to malaria-endemic areas.

Parasites (sporozoite stage) are injected into the skin capillaries by a female *Anopheles* sp. mosquito. From there they travel via the bloodstream to the liver, where they develop and multiply in liver cells before entering the blood stream again (merozoite stage) and invading for further reproduction. From there other internal organs, e.g. the brain, can be affected as clumps of infected erythrocytes start blocking capillary blood flow.

### 1.2 Epidemiology

Malaria affects 40% of the world's population with more than 1 million deaths annually. This represents a tremendous human suffering and a burden that prevents the development of the affected endemic communities. Malaria is one of the world's greatest public health problems particularly affecting young children and pregnant women in the poorest areas of sub-Saharan Africa.

The increasing emergence of insecticide resistant vectors and drug resistant parasites calls for investment in new and better control tools. Malaria vaccines hold the potential to dramatically alleviate the burden of malaria. However, our understanding of the mechanisms underlying protective immunity is incomplete and specific markers of protection still needs to be defined.

Clinical malaria is caused by the cyclical proliferation of the asexual stages of *Plasmodium falciparum* in red blood cells. Malaria mortality is primarily due to organ dysfunction in particular of the brain, following sequestration in the micro-vasculature by infected red blood cells.

An effective malaria vaccine will require the induction of appropriate humoral and cellular immune responses, against several key parasite antigens expressed during the various stages of the parasite life cycle. Each stage in the life cycle provides an opportunity for a vaccine.

It is a well-established observation that repeated exposure to malaria parasites can lead to the development of solid clinical immunity. Clinically immune individuals generally have a lower parasite density and the immunity is effective at reducing mortality. An a-sexual stage blood stage vaccine will induce immunity that controls parasitemia and therefore prevent clinical complications increasing the risk of death.

### **1.3 Prevention and Control of Infection among Humans**

There are several reasons why malaria remains to be one of greatest health problems. One of the main reasons is failure to achieve adequate coverage with, and reduced pricing of, existing tools such as drugs and insecticide-treated bednets. There is user ignorance of how to use these tools. The decreasing effectiveness of existing tools (e.g. emergence of drug resistance, particularly to chloroquine and sulphadoxine-pyrimethamine, and, in south-east Asia, resistance to third-and fourth-line antimalarials; resistance to insecticides, including pyrethroids) is a major challenge. The availability of an efficacious malaria vaccine would certainly be a major achievement to overcome the failures of the current control strategy.

### **1.4 Name and description of the investigational product**

Apical membrane antigen 1 (AMA-1) is considered one of the leading candidates for inclusion in a vaccine against blood stages of *Plasmodium falciparum*. AMA-1 is a Type I integral membrane merozoite protein that is implicated in the process of invasion of host erythrocytes.

AMA-1 of *P. falciparum* (PfAMA-1) the product of a single, essential gene, is initially localised on the apical invasion organelles of the merozoite. It subsequently undergoes proteolytic processing and relocalisation to the merozoite external membrane. AMA-1 has structural homologues in all species of malaria studied to date as well as in *Toxoplasma gondii*. Important determinants of protein structure, such as the position of cysteine residues, are well-conserved between species.

PfAMA-1 has an apparent molecular weight on SDS-PAGE of 83kDa, and comprises 622 amino acids containing 16 cysteine residues. Based on disulphide bonding a domain structure has been assigned to the molecule (see Figure 1).

Figure 1 : Disulphide bonding in *P. falciparum* AMA-1 defines the pro-sequence and domains I, II and III. *SP* (signal peptide), *TM* (transmembrane region)

[figure not shown]

AMA-1 is a malaria vaccine candidate for the following reasons:

AMA-1 appears to be immunogenic in populations naturally exposed to malaria infection

Antibodies against AMA-1 (induced by immunisation with AMA-1 or purified from the serum of naturally exposed subjects) block merozoite invasion of red blood cells *in vitro*

Vaccination with either AMA-1 purified from merozoites, or with AMA-1 produced by recombinant expression, has protected mice and primates from malaria

Passive transfer of antibodies against AMA-1 has protected mice against malaria

When AMA-1 undergoes chemical reduction, to destroy disulphide bonds, it loses the ability to induce functional antibodies. Eukaryotic secretion expression systems can provide recombinant proteins with the correct disulphide bonding without the need for protein refolding. [name] and colleagues therefore selected the yeast, *Pichia pastoris*, for AMA-1 production. *P. pastoris* has already been used by [name] to produce AMA-1 of *P. vivax*. This material induced antibodies that inhibited parasite invasion and was immunogenic in rhesus monkeys.

*P. falciparum* has a codon usage highly biased to A and T and, as a result, *P. pastoris* was not able to utilise the native *P. falciparum* AMA1 gene. In collaboration with colleagues at NIMR in London, UK, an alternative AMA-1 gene was designed and synthesised. This artificial gene is based on the codon usage of *P. pastoris*. The native AMA-1 protein, as found in merozoites, does not appear to be N-glycosylated. However, *P. vivax* AMA-1 expression using an unmodified gene resulted in heterologous product formation due to glycosylation. To obtain a homogenous product, the 6 potential N-glycosylation sites occurring in *P. falciparum* AMA-1 were substituted with amino acids naturally occurring in AMA-1's from other strains of *P. falciparum* or other *Plasmodium* species.

Using this artificial gene, large amounts of AMA-1 have been produced at BPRC from series of recombinant yeast. Because it is not known which domains of AMA-1 mediate the induction of parasite inhibitory Ab, efforts have focused on expression of the AMA-1 ectodomain comprising pro-sequence (without the signal peptide) and domains I, II and III, with a stop just N-terminal of the transmembrane region. A construct, *Pf4mH* (comprising *PfAMA-1* amino acids 25-544, a myc epitope and a Hexa-His epitope) was prepared to provide a readily purified protein suitable for initial analyses.

Subsequently the construct *Pf11.0* (comprising only *PfAMA1* amino acids 25-545) was prepared to provide material for clinical evaluation. Fermentation and purification of *Pf11.0* have been developed to provide a process delivering a product with a highly purified active ingredient under GMP.

A large number of AMA-1 haplotypes are known to exist. The effects of this diversity on vaccine performance are unknown. The FVO strain was selected for expression based on its sequence diversity from the 3D7 strain that was being used by other researchers.

## 1.5 Summary of findings from non-clinical studies

### 1.5.1 Antigenicity:

Antigenicity of *Pf4mH* was evaluated by ELISA (Figure 2) using *PfAMA-1*-specific mAbs 4G2 (recognising a conformational epitope in the ectodomain and capable of blocking parasite multiplication *in vitro*), 58F8 (recognising a linear epitope in the N-terminal region of *PfAMA-1*), and 28G2 (recognising a linear epitope within the cytoplasmic C-terminal region of *PfAMA-1*), and endemic human serum from Guinea-Bissau (antibodies in naturally exposed human subjects are predominantly directed towards conformational determinants of *PfAMA-1* that are dependant on disulphide bonding). As expected, mAb 28G2 and human serum from uninfected European donors are non-reactive with *Pf4mH*. mAb 58F8 displays strong reactivity. *Pf4mH* is well recognised by the conformational, parasite-inhibitory mAb 4G2 and by antibodies in human serum from a malaria endemic region, demonstrating an authentic antigenic profile.

Figure 2 : Antigenicity of Pichia-expressed *PfAMA-1*

[figure not shown]

### 1.5.2 Immunogenicity:

Rabbit polyclonal antisera were prepared by injection of 100 µg purified *Pf4mH* (Rabbits 678, 679 and 680) using Freund's complete adjuvant, followed by 3 further injections of 100 µg at days 14, 28 and 56

using Freund's incomplete adjuvant. Antisera obtained 4 weeks after the last injection were tested for reactivity by ELISA and immunofluorescence (IFA).

| Rabbit | ELISA titre  | IFA titre  |                       |
|--------|--------------------------|------------------------|-----------------------|
|        | Pf 4mH            | FCR3                   | NF54                  |
| 678    | 55765                    | 2.5 x 10   | 1.3 x 10  |
| 679    | 27753                    | 2.5 x 10   | 0.6 x 10  |
| 680    | 12663                    | 1.3 x 10   | 0.3 x 10  |

1. Titres are represented as the reciprocal dilution at which an OD of 1.0 is obtained. For an approximate conversion this to end point titres, multiply by 40

2. End point titres

Antibodies from sera obtained 4 weeks after the final immunisation were purified on protein A columns using standard protocols, extensively dialysed against RPMI 1640, filter-sterilised and used in the *Plasmodium* inhibition assay (PIA) (Figure 3).

**Figure 3: *Plasmodium* inhibition assay (PIA) :**

[figure not shown]

The effect of purified IgG on parasite invasion was evaluated using *in vitro* matured *P. falciparum* schizonts at a starting parasitemia of 0.5-1%, a haematocrit of 3.0% and a final total volume of 150 µl in standard culture medium. Radiolabel (hypoxanthine) was added after 17 hours of incubation. Parasites were harvested 10 hours later and incorporation of label was determined. Parasite growth inhibition, reported as a percentage, was determined as follows:

$$100 - ((\text{average CPM}_{\text{experimental}} / \text{average CPM}_{\text{control}}) \times 100).$$

The incorporation for erythrocytes alone was subtracted from all averages prior to determining the percentage inhibition. Control IgG was isolated from rabbits that had been immunised according to the same scheme with adjuvant only. The average of five PIA's for Rb 678, 679 and 680 IgG at 1.5 (●) and 0.75 mg/mL (○) is shown.

### **1.5.3.2 Immunogenicity in rhesus macaques**

Serum was obtained from the 24 macaques during the study and antibody responses were assessed. Figure 4 and 5 show that AMA-1 induces antibodies in rhesus macaques. Before vaccination all animals had titres close to the lower detection limit of the assay (0.03, 0.02 to 0.05 µg/mL mean 95% CI). Following vaccination titres increased significantly in all groups ( $P < 0.001$ ). There were no differences in the amount of antibody elicited by the two dosages (Figure 4). The kinetics of antibody response was fastest in the Alhydrogel group where all monkeys responded well after the first vaccination. In contrast, the ISA and AS02A groups required two immunisations in order to observe responses  $> 10$  µg/mL IgG in all monkeys. At day 14 and day 28, IgG titres were significantly lower in the AS02A group as compared to the Alhydrogel group (0.04 fold, 95% CI 0.01 - 0.13 and 0.02 fold, 95% CI 0.00 - 0.17, respectively). This observation was, although not statistically significant, also made at day 42, when titres in the AS02A group were about 0.52 fold lower 95% CI (0.25 - 1.06). At day 84 titres in the Alhydrogel and AS02A groups were similar, whereas titres in the Montanide ISA 720 group were 1.83 fold higher 95% CI (0.63 - 5.36). At day 98, the lowest titres were measured in the Alhydrogel group. Titres were higher in the AS02A and Montanide ISA 720 groups 2.04 fold (0.50 - 8.41) and 3.86 fold (0.94 - 15.88), respectively.

Before vaccination all animals were IFA-antibody negative (data not shown). Two weeks following the third vaccination all animals had developed IFA-antibodies (data not shown). As was observed for IgG levels, dose had no apparent effect on IFA titres. Adjuvant did, although not statistically significant, appear to influence IFA titres. The lowest titres were observed in the Alhydrogel group, followed by

the AS02A group. The highest IFA titres were observed in the Montanide ISA 720 group (data not shown).

**Figure 4: The effect of antigen dose (10 or 50 µg) on IgG levels**

[figure not shown]

**Figure 5: The effect of adjuvant on IgG Levels**

[figure not shown]

## 1.6 Summary of previous clinical trials

Three phase 1 clinical trials are ongoing, with different formulation of AMA-1 antigen. One trial is assessing *Escherichia coli* recombinant AMA-1 vaccine from the Walter Reed Army Institute of Research, United States. Two trials are evaluating a *P. pastoris*-expressed AMA-1. One of these comprises a chimera of MSP1-AMA-1. No published results of those trials are available.

## **1.7 Rationale**

### **1.7.1 Risks and benefit to human subjects**

The sterility of the product and the absence of toxicological effects are guaranteed by the results of the quality controls performed by Eurogentec and the pharmaco-toxicological study performed by NOTOX.

Safety of the vaccine in rhesus macaques has been tested and no vaccine-related severe adverse events were observed.

### **1.7.2 Rationale for adjuvant selection**

- i. Alum, is most widely used and generally accepted for use in human vaccines. Results in other malaria vaccine trials show that good immune responses can be obtained
- ii. Montanide ISA 720 is approved for use in humans. Results in previous malaria vaccine trials have shown excellent immune responses with acceptable safety profiles;
- iii. AS02A, which has been developed by GSK, is an oil/ water emulsion containing MPL® and QS21. Most of the data on AS02A adjuvant has been from clinical trial using the RTS,S antigen . The RTS,S antigen is a fusion protein composed of a circumsporozoite based antigen and hepatitis b surface antigen. The candidate RTS,S/AS02A malaria vaccine has been used in phase I/II clinical trials in malaria-naïve adults in Belgium and the USA and semi-immune (malaria-experienced) adults in The Gambia and Western Kenya. The vaccine has also been used in paediatric clinical trials in children aged 1-11 years in The Gambia and Mozambique.

To date, at least 481 adult subjects have received over 1250 doses of the RTS,S/AS02A malaria vaccine. 60 children aged 6-11 years have received 179 doses of RTS,S/AS02A and 1825 children aged 1-5 years have received 5284 dose of RTS,S/AS02A .

The reported adverse events following vaccination in children have been pain and swelling at the injection site, loss of appetite, upset stomach, fever, fussiness and tiredness. In generally these adverse events have been transient lasting generally for two days and mainly mild to moderate in intensity. In adults, the most frequently reported adverse events have been pain, myalgia and fatigue and transient resolving usually within 4 days. Severe adverse events were infrequent and resolved or decreased in intensity within 2 days.

To date AS02A-containing vaccines did not elicit any serious adverse events that necessitated the withdrawal of the vaccine from clinical use...

### **1.7.3 Rationale for dosage selection:**

Previous studies have shown that a dosage of 300 µg of malaria antigens (MSP-1, MSP-2 and RESA) in Montanide ISA 720 gave rise to local discomfort leading to transient limitations in activities of daily living (0). Studies with GLURP indicate that a 100 µg dosage either in Alum or Montanide ISA 720 frequently gave rise to local reactions ([name] pers comm.). Given these considerations, it was decided to use a maximum dose of 50 µg. A dosage of about 50 µg of malaria antigens in Montanide ISA 720 appears to be immunogenic, whilst giving only mild to moderate (local) reactogenicity (0, 0).

[figure not shown]

## 2 TRIAL OBJECTIVES

### 2.1 Primary Objective

**To evaluate the safety** of 3 doses given at D0, D28 and D112 of 2 different dosages of AMA-1 (10 µg or 50 µg ) adjuvanted either with Alhydrogel or AS02A or Montanide ISA 720 in healthy adults not previously exposed to the parasite *Plasmodium falciparum*. The safety and the tolerability of the vaccine will be assessed on the rate of solicited and unsolicited events/reactions. The safety profile will include local and systemic reactions/events as well as the biological safety, based on a clinically significant change of the baseline value of the main biological criteria.

### 2.2 Secondary Objectives

#### 2.2.1 Humoral Immune Response

**To assess the humoral response** to the vaccine antigens (PfAMA-125-545). The antibody response will be measured by ELISA and IFA.

- 

#### 2.2.2 Cellular immune response

**To assess the cellular immune response** T cell proliferation will be measured following in vitro stimulation with the vaccine antigen and parts thereof. Cytokine production will be assayed by ELISPOT for the cytokines IL-4 and IFNγ following in vitro stimulation with the vaccine antigen.

### 2.3 Exploratory Objective(s)

To assess the quality of the humoral immune response by measuring

- IgG1, IgG2, IgG3, IgG4 subclasses
- The domain specificity of the response
- The broadness (allele specificity of the response)
- The ability to block parasite growth in vitro
- The ability to recognise the moab 4G2 binding site and recognition of 4G2 mimotopes
- IgG avidity
- 

## 3 TRIAL DESIGN AND METHODOLOGY

### 3.1 Trial design

#### 3.1.1 Description and Justification of the Trial Design

The trial is a single-blind, randomised, dose escalating, unicentre trial. Three different adjuvants will be assessed, Alum, Montanide and AS02A. Two different dosages – 10µg and 50µg – of AMA-1 will be evaluated for each adjuvant. Six groups of 10 volunteers will be included. The groups are the following:

| Group | Adjuvant          | Dosage | Number of subjects |
|-------|-------------------|--------|--------------------|
| Al10  | Alum              | 10µg   | 10                 |
| Al50  | Alum              | 50µg   | 10                 |
| M10   | Montanide ISA 720 | 10µg   | 10                 |
| M50   | Montanide ISA 720 | 50µg   | 10                 |
| Ao10  | AS02A             | 10µg   | 10                 |
| Ao50  | AS02A             | 50µg   | 10                 |

The clinical, biological and immunological data, when collected after immunization, will be mainly compared to the baseline of each subject. The trial is not designed to allow a comparison between groups. Thus, a formulation will be considered for future clinical trial only if the rate of adverse events/reactions deemed to be vaccine related, is found to be at the same range as routine vaccine in adults, i.e. events/reactions < 10% (The sample size used does not allow for 10%, but rather 25%). Furthermore, the dosage choice will be based on the level and the functionality of the immune response as well as the persistence of the immune response.

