### 7.4.2 Determination of the Sample Size

The total number of subject will be 60. A total of 6 groups of 10 subjects per group will be recruited. It is not expected to have loss to follow-up.

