### **7.4.4 Statistical Methods**

The analysis shall be descriptive; the sample size does not allow any comparison between groups. For categorical variables, frequency distributions, by vaccination group, will be presented. For continuous variables, box-whisker plots, medians, inter-quartile ranges and ranges will be presented by vaccination group.

The analysis plan will be available before the lock of the data base for the interim analysis after the second injection of vaccine.

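### Section 3.1.1 bases the dosage choice on immune response but rules out group comparisons, and the planned output gives no dosage difference or its uncertainty

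*Protocol*

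**What the plan says.** Section 3.1.1 sets up six groups of 10: three adjuvants, each at 10 µg and 50 µg. It states that "The trial is not designed to allow a comparison between groups". Two sentences later it gives the basis for selecting a dosage: "the dosage choice will be based on the level and the functionality of the immune response", together with how long that response persists. It names no deciding assay, day or size of difference, does not say whether adjuvants are pooled, and does not say what follows if the dosages look alike. The reference it gives for the data is within-subject: "The clinical, biological and immunological data, when collected after immunization, will be mainly compared to the baseline of each subject".

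Section 7.4.4, echoed in the Synopsis under Statistical Methods, says: "The analysis shall be descriptive; the sample size does not allow any comparison between groups". It then fixes the display for immune measurements: "For continuous variables, box-whisker plots, medians, inter-quartile ranges and ranges will be presented by vaccination" group.

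On prior evidence, section 1.5.3.2 reports for macaques given the same two dosages in the same three adjuvants: "There were no differences in the amount of antibody elicited by the two dosages". It also reports no apparent effect of dosage on IFA titres.

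**The concern.** Al10 and Al50, M10 and M50, Ao10 and Ao50 are pairs of groups in the table of section 3.1.1. Preferring one dosage over the other on immune response means comparing the members of these pairs. Change from each subject's own baseline does not avoid this, because the choice still turns on how the change differs between groups. The protocol therefore gives the data a use that its analysis section says they cannot support, and fixes an output without the quantity that the choice needs.

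What is at stake is the dosage taken into later trials. A gap between two groups of 10 could be read as a dosage effect when the data do not separate the dosages, or a real difference could be read in the wrong direction. The macaque result makes equal dosages a realistic case. The primary safety objective is not affected.

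**Working it through.** **The plan's own figure.** "A total of 6 groups of 10 subjects per group will be recruited": 6 × 10 = 60. This reproduces as arithmetic only. No SD, effect size, power or alpha is given for any immune endpoint.

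**Inputs.**
- 10 subjects per group, hence 30 per dosage across the three adjuvants (sections 3.1.1 and 7.4.2). No loss to follow-up is expected (7.4.2).
- Spread of IgG: not given for humans, so an assumption. It is back-calculated from the macaque fold-ratio intervals between adjuvants in section 1.5.3.2, taking 24 animals / 3 adjuvants = 8 per adjuvant and t on 21 df = 2.08.

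**Step 1: SD of log10 IgG** = [log10(upper/lower)/2] / [2.08 × √(2/8)].
- Day 42, 0.25 to 1.06: 0.314 / 1.04 = 0.30
- Day 84, 0.63 to 5.36: 0.465 / 1.04 = 0.45
- Day 98, 0.94 to 15.88: 0.614 / 1.04 = 0.59

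The working range is 0.30 to 0.60.

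**Step 2: chance gaps when the dosages are equal.** Two samples of 10 normal log10 values with the same mean were simulated. The count is how often the medians differ by at least log10(2) = 0.301 in either direction (p). For at least one of three adjuvants the formula is 1 − (1 − p)³.

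| SD (log10) | p, one adjuvant | at least one of three |
|---|---|---|
| 0.30 | 0.056 (6%) | 16% |
| 0.45 | 0.203 (20%) | 49% |
| 0.60 | 0.341 (34%) | 71% |

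**Step 3: what an interval would show.** The 95% interval for the 50:10 ratio is the estimate multiplied or divided by 10^(t × SD × √(2/n)).
- Within an adjuvant, n = 10, 18 df, t = 2.10: 10^(2.10 × 0.30 × 0.447) = 1.9, up to 10^(2.10 × 0.60 × 0.447) = 3.7.
- Adjusted for adjuvant, n = 30 per dosage, 60 − 4 = 56 df, t = 2.00: 10^(2.00 × 0.30 × 0.258) = 1.4, up to 10^(2.00 × 0.60 × 0.258) = 2.0.

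The standard error falls by 1 − √(10/30) = 42%.

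**Step 4: if a real difference exists.** This step needs a selection rule, and the protocol states none. Suppose, for illustration only, that the higher of two medians of 10 were followed. At ln SD 0.7, 1.0 and 1.35 (divided by 2.303, log10 SD 0.30, 0.43 and 0.59), the less immunogenic dosage would be followed in 14%, 22% and 29% of trials when the true ratio is 1.5, and in 3%, 9% and 16% when it is 2.

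**The case against.** **The planned display shows spread.** This is correct. Box plots, inter-quartile ranges and ranges are planned, and heavily overlapping boxes warn a careful reader. A reader might infer that only medians are shown; section 7.4.4 does not support that. What is absent is an estimate of the dosage difference and its uncertainty.

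**No pick-the-higher rule is written.** Also correct. A reader might infer that the higher median always wins, so that the dosage is picked by chance when the two are equal. Section 3.1.1 names three considerations, after an adverse-event criterion for the formulation, which reads more like a judgement over several results. A coin-toss choice between truly equal dosages would in any case cost nothing in immunogenicity, and it would arise under a pick-the-higher rule at any sample size. The point rests on the contradiction and on the size of chance gaps.

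**This belongs to the analysis plan.** Section 7.4.4 promises one before the interim database lock, and models and timepoints usually sit there. But the protocol fixes both the use of the data and an analysis without comparison. An analysis plan that follows 7.4.4 could not supply the contrast that 3.1.1 needs.

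**The pooled contrast is not clean.** This stands in part. The 10 µg doses come first (3.2.1, 6.2.2). Section 3.1.2 allows randomisation in two blocks of 30 if recruitment is short, and if those blocks follow the dosage steps, which is not stated, dosage would be confounded with enrolment time. Physicians know the dose (3.1.3), and technicians may infer it from a dated vial (3.4.3). Reading the planned summaries side by side has the same weaknesses.

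**Conclusion.** The contradiction stands on the text of 3.1.1 and 7.4.4 alone and needs no numerical assumption. The dosage choice requires a between-group contrast that the protocol rules out and does not estimate.

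The size depends on the assumed SD. Over log10 SD 0.30 to 0.60, a two-fold or larger chance gap in medians appears in 6% to 34% of trials per adjuvant (16% to 71% in at least one of three). Intervals would be a factor of 1.9 to 3.7 within an adjuvant and 1.4 to 2.0 adjusted across adjuvants. The range rests on macaque spread, on 8 animals per adjuvant and on log-normal IgG; human spread could lie outside it. The adjusted figure also assumes a similar dosage effect in each adjuvant.

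The documents do not show that a dosage would be chosen at random, and nothing here bears on which dosage is right. The change should be made because the choice feeds later trials.

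**What to change.** Reconcile sections 3.1.1 and 7.4.4, and the matching Synopsis line, in one of two ways.

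1. State that this trial will not select a dosage and that the immune results are descriptive only.
2. Keep the dosage choice, with an analysis limited to estimation. For log AMA-1 IgG at D140 (level) and D365 (persistence), report the three within-adjuvant 50:10 µg geometric mean ratios with 95% confidence intervals, and the adjuvant-adjusted ratio (30 v 30) from a linear model with dosage and adjuvant. Report the same contrasts for the Plasmodium inhibition assay, on its own scale and at the same days, so that functionality is covered. State that an interval that includes no difference is reported as dosages not distinguished. Label the pooled contrast as assuming a similar dosage effect across adjuvants and, if the two-block fallback is used with 10 µg given first, as potentially confounded with enrolment time.

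The wording should not prescribe which dosage follows from any result.

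The cost is a few lines of text and, under the second option, small models on samples already scheduled in sections 7.2.1 and 7.3. One scheduling detail needs settling: section 7.3 lists the inhibition assay at D365, but the growth-inhibition row of the flow chart is not marked for that visit.
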